# Efficacy of Real-Time Feedback Exercise Therapy in Patients Following Total Hip Arthroplasty: Protocol for a Pilot Cluster-Randomized Controlled Trial

**DOI:** 10.2196/59755

**Published:** 2024-08-20

**Keywords:** hip replacement, exercise therapy, real-time feedback, movement analysis

## Abstract

**Background:**

Osteoarthritis of the hip joint is an increasing functional and health-related problem. The most common surgical treatment is hip replacement to reduce pain and improve function. Rehabilitation after total hip arthroplasty (THA) is not regulated in Austria and mostly depends on the patient’s own initiative and possibilities. Functional deficits, such as valgus thrust of the leg, functional Trendelenburg gait, or Duchenne limp, are characteristic symptoms before and, due to the performance learning effect prior to surgery, also after the operation. Addressing these deficits is possible through neuromuscular-focused exercise therapy. The efficacy of such therapy relies significantly on the quality of performance, the frequency of exercise, and the duration of engagement. Enhancing sustainability is achievable through increased motivation and real-time feedback (RTF) on exercise execution facilitated by digital feedback systems.

**Objective:**

This study will be performed to quantify the medium-term effectiveness of digital home exercise feedback systems on functional performance following THA.

**Methods:**

A clinical trial with a cluster-randomized, 2-arm, parallel-group design with an 8-week intervention phase and subsequent follow-ups at 3 and 6 months postsurgery will be conducted. Feedback during exercising will be provided through a blended-care program, combining a supervised group exercise program with a self-developed digital feedback system for home exercise. In total, 70 patients will be recruited for baseline. The primary outcome parameters will be the frontal knee range of motion, pelvic obliquity, and lateral trunk lean. Secondary outcomes will be the sum scores of patient-reported outcomes and relevant kinematic, kinetic, and spatiotemporal parameters.

**Results:**

The trial started in January 2024, and the first results are anticipated to be published by June 2025. RTF-supported home exercise is expected to improve exercise execution quality and therapeutic adherence compared to using paper instructions for excise guidance.

**Conclusions:**

The anticipated findings of this study aim to offer new insights into the effect of a blended-care program incorporating digital RTF on exercise therapy after unilateral THA, in addition to knowledge on the functional status 3 and 6 months postsurgery, for further improvement in the development of rehabilitation guidelines following THA.

**Trial Registration:**

ClinicalTrials.gov: NCT06161194; https://clinicaltrials.gov/study/NCT06161194

**International Registered Report Identifier (IRRID):**

PRR1-10.2196/59755

## Introduction

### Background

Osteoarthritis (OA) of the hip has become an increasing burden for patients, with a high impact on the socioeconomic system [1]. The prevalence of hip OA in the population aged over 45 years is 19 % in women and 27 % in men [2]. The main factors contributing to the development and progression of hip OA, such as obesity, nutrition, sociodemographic setting, injuries, or joint shape, have been extensively studied [3,4]. Further biomechanical aspects related to overload of the cartilage [2] induced by a sum of loads have been identified. Deciding to undergo conservative exercise treatment or surgical total hip arthroplasty (THA) and identifying the best time point for THA can be difficult due to low-level evidence [5]. In Austria, a total of 18,052 primary THAs and 1290 reimplantation surgeries were performed in 2015 [6]. Despite the significant number of THAs, there is a notable deficiency in guidelines and recommendations for both pre- and postoperative management, particularly in the context of functional restoration [7,8]. Notably, Austria lacks a nationally implemented postsurgery patient pathway. However, to some extent, there is existing knowledge on the effectiveness of exercise therapy in reducing functional deficits after THA, as evidenced by previous studies [9-11]. In particular, following motor re-education approaches [12-14] and enhancing the sustainability of exercising by means of real-time feedback (RTF) have been proposed in several studies [15-17]. Regarding motor re-education, the quality of performance, compliance, and adherence to exercising are essential. However, there is no system available focusing on the relevant functional deficits for RTF-supported home exercise. These deficits are valgus thrust, which is defined as the bowing in of the knee or abrupt worsening of the dynamic valgus [18], and pelvic drop, which is increased lowering of the contralateral pelvis side during dynamic single-leg stance (SLS) phases [19]. Additionally, lateral trunk lean is also addressed in the context of such functional deficits. In contrast to the neurologically induced Duchenne limp, this dynamic functional deficit can, among other factors, be induced by pain [20]. Furthermore, there is a lack of kinematic and especially kinetic 3D data addressing functional deficits during recovery after THA [9,10,21,22]. Therefore, the aim of this trial is to investigate the effect of RTF-supported home exercise compared to written home exercise instructions on the recovery of functional performance after THA. Specifically, we want to analyze the improvement of functional deficits at 3 and 6 months postsurgery using quantifiable three-dimensional movement analysis (3DMA) of activity-of-daily-living (ADL) tasks.

### Study Goals

This pilot cluster-randomized, 2-arm, parallel-group controlled trial aims at enhancing the understanding of the effects of RTF on functional deficits such as knee valgus thrust, pelvic drop, and lateral trunk lean after THA. Biomechanical and patient-reported outcomes will be assessed prior to the intervention, as well as at 3- and 6-month follow-ups postsurgery.

The primary research question is whether blended-care digital RTF-supported home exercise (intervention group [IG]) leads to significant higher improvements in the control of the frontal knee range of motion (RoM), pelvic obliquity, and lateral trunk lean compared to blended-care exercise supported by written instructions (control group [CG]) as a comparator. The secondary aspect will focus on potential differences between groups concerning aspects of the quality of life, function, and physical activity. Tertiary functional outcomes between groups will be compared to quantify movement quality. Consequently, the underlying primary null hypotheses were prespecified as follows:

Improvements in the frontal knee RoM are equal between the IG and the CG.Improvements in pelvic obliquity are equal between the IG and the CG.Improvements in lateral trunk lean are equal between the IG and the CG.

In addition, the primary alternative hypotheses are as follows:

Improvements in the frontal knee RoM are not equal between the IG and the CG.Improvements in pelvic obliquity are not equal between the IG and the CG.Improvements in lateral trunk lean are not equal between the IG and the CG.

The 3 primary outcomes (frontal knee RoM, pelvic obliquity, and lateral trunk lean) will be tested in 3 independent hypotheses (each parameter will be tested independently of the others in 2 follow-ups).

Secondary hypotheses will be tested independently for differences between the IG and the CG in a series of metric patient-reported outcomes measures (PROMs): (1) the Harris Hip Score (HHS), (2) the Hip Osteoarthritis Outcome Score (HOOS), (3) the 12-item Short Form Health Survey (SF-12), (4) the International Physical Activity Questionnaire – Short Form (IPAQ-SF), and, if applicable, (5) the Knee Injury and Osteoarthritis Outcome Score (KOOS).

Tertiary hypotheses will be tested independently for differences between the IG and the CG in a series of metric movement analysis outcomes, including (1) kinematics, (2) kinetics, and (3) spatiotemporal results.

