#### Analyzed Data

The parameters related to locomotion tasks will be normalized to gait and stance phases. The stance phase will be defined between the heel-strike and toe-off of the observed leg. Cyclic tasks will be normalized to start, turn, and end events. The circuit task TuG will be split into sit-to-walk, straight walking, turn, and walk-to-sit. STS and STSr will be analyzed according to the literature using the lift-off event. The ADL task SQL will be spatially defined by start, turn, and end events. During the exploration of the database, new variables will be calculated and reported.

Kinematic data will be time-normalized from heel strike to heel strike, and kinetic data will be time-normalized from heel strike to toe-off. Individual participant data will be expressed as an average per condition. Time normalization, data processing, and parameter calculations will be conducted using self-developed scripts in MATLAB 2018a (Mathworks). The analyzed data will be stored as single cycles, averaged cycles, and single data at certain time points in a .mat file. With the help of a self-written MATLAB tool, these .mat files will be made searchable with arbitrary filter settings. All data can also be used in future analyses according to the latest scientific knowledge.

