### Statistical Analysis

Data will be inspected for outliers using boxplots. Shapiro-Wilk tests and additional graphical inspections of q-q plots will be applied to test for the normality assumption. Metric baseline characteristics will be indicated as means (SDs) and categorical baseline characteristics as frequencies (n, %). Unadjusted outcome scores will be reported as means (95% CIs). People from the same cluster tend to be more similar than those from different clusters, and the analysis must allow for this. A common enhancement is to apply a linear mixed effects model with the cluster specified as a random intercept. To model changes between baseline and follow-up, we will include baseline measurements as covariates. Following suggestions by Klar and Darlington [37], we will adjust for each participant’s baseline assessment and for the baseline cluster mean. Otherwise, no adjustments for covariates are foreseen. Treatment effects will be reported independently for follow-up t_1_ and follow-up t_2_, including unstandardized and standardized regression coefficients as effect estimates, standard errors, *t* statistics, and appropriate *P* values via the Satterthwaite degrees-of-freedom method. Between-cluster and residual variances will be reported for all outcomes. In the case of severe outliers or major violations of the normality assumption, logarithmic data transformation approaches will be explored. Outcome parameters on the ordinal scale will be analyzed descriptively and reported as medians with ranges. All descriptive statistics and corresponding numbers of subjects (n, %) will be reported, along with losses to follow-ups. Effect sizes will be calculated and reported accordingly (per protocol). In addition, the hypotheses will be analyzed according to the intention-to-treat principle (last value carried forward), providing a more conservative effect estimate [38] when missing observations introduce bias. The α value will be set to .05, and exact 2-sided *P* values will be reported. Hypotheses will be tested independently of each other. The 2-armed study design does not require post hoc tests, so no adjustment for familywise α error accumulation is needed.

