## Results

The trial started in January 2024, and the first results are anticipated to be published by June 2025. Based on the knowledge from comparable (to some extent) studies on RTF effectiveness in motor re-education conditions, we expect that RTF-supported home exercise will tend to be more effective compared to using paper instructions for exercise guidance. This effect might be reported for all 3 hypotheses (functional deficits, quality of life, and activity questionnaires), as well as biomechanical parameters.

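### Secondary and tertiary outcomes are formal between-arm hypotheses at full alpha, with no gatekeeping or exploratory label, and the two-arm reason for waiving adjustment does not cover them

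*Protocol article*

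**What the plan says.** All references are to the protocol article.

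- **Study Goals** writes out null and alternative hypotheses for the three primary outcomes, then adds two further tiers. For the PROMs: "Secondary hypotheses will be tested independently for differences between the IG and the CG in a series of metric patient-reported outcomes measures (PROMs"), namely HHS, HOOS, SF-12, IPAQ-SF and, if applicable, KOOS. For the movement data: "Tertiary hypotheses will be tested independently for differences between the IG and the CG in a series of metric movement analysis outcomes", covering kinematics, kinetics and spatiotemporal results.
- **Statistical Analysis** sets one threshold, "The α value will be set to .05", with two-sided P values and treatment effects reported separately for t1 and t2. It states "Hypotheses will be tested independently of each other" and gives this reason for not adjusting: "The 2-armed study design does not require post hoc tests, so no adjustment for familywise α error accumulation is needed".
- **Analyzed Data** adds "During the exploration of the database, new variables will be calculated and reported".
- **Results** anticipates: "This effect might be reported for all 3 hypotheses (functional deficits, quality of life, and activity questionnaires), as well as biomechanical parameters".

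No section makes a secondary or tertiary test conditional on a primary result, and none calls either tier exploratory or descriptive. The only descriptive carve-out is for outcomes on an ordinal scale.

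**The concern.** The waiver rests on the wrong ground. Having two arms removes multiplicity from comparing several pairs of arms. It does nothing about many outcomes, each tested at two visits. Because the article rules adjustment out for this stated reason, this is a stated rule with a faulty basis and not a detail left to a later document.

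The consequence lies in what the trial may conclude. If all three primary outcomes are null, the text still permits a significant PROM or gait parameter to be reported as an effect of real-time feedback, on the same .05 footing as a primary hypothesis. The Results section already sets quality of life and activity questionnaires beside the primary functional deficits as places where an effect might be reported. The abstract's conclusions say that the findings are meant to help develop rehabilitation guidelines, so the distinction between confirmed and suggestive results matters.

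**Working it through.** **The plan's own figures.** The article gives no familywise error rate to reproduce. Its one operating characteristic is a power of 0.75 for 24 per group, d = 0.8, clusters of 3 and ICC 0.05. The design effect is 1 + (3 − 1) × 0.05 = 1.10 and the effective n is 24 / 1.10 = 21.8 per arm. The normal approximation then gives a power of 0.752. This reproduces the stated value and is not in dispute. It also shows that the .05 in the sample size section is the alpha of a single comparison.

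**Inputs from the article.** Alpha .05, two-sided, per test; 4 PROMs, or 5 with KOOS; 2 follow-ups. Hence 4 × 2 = 8 or 5 × 2 = 10 secondary tests.

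**Inputs assumed.**
- The correlation between test statistics is not given. I take a common value ρ of 0, 0.5 or 0.8.
- The tertiary count is not given. For illustration I take one parameter in each of 3 classes, for each of the 9 recorded tasks (level walking, TuG, STS, STSr, squat lifting, ramp up, ramp down, stair up, stair down), at 2 visits: 3 × 9 × 2 = 54 tests.

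**Formula.** With no true effect and independent tests, the chance of at least one false positive among k tests is 1 − 0.95^k. For equally correlated z statistics it is 1 − ∫ φ(u) [Φ((1.96 − √ρ·u)/√(1−ρ)) − Φ((−1.96 − √ρ·u)/√(1−ρ))]^k du, evaluated numerically.

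| Set | k | ρ = 0 | ρ = 0.5 | ρ = 0.8 |
|---|---|---|---|---|
| SF-12 alone, 2 visits | 2 | 9.8% | 9.1% | 7.8% |
| PROMs without KOOS | 8 | 33.7% | 25.0% | 15.7% |
| PROMs with KOOS | 10 | 40.1% | 28.7% | 17.3% |
| Tertiary, one parameter per class | 6 | 26.5% | 20.7% | 13.9% |
| Tertiary, assumed 54 tests | 54 | 93.7% | 64.0% | 30.5% |

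For the assumed 54 tests the expected number of false positives is 54 × 0.05 = 2.7, whatever the correlation.

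**Cross-check.** A multivariate-normal simulation with separate correlations between outcomes (0.2 to 0.7) and between visits (0.5 to 0.7) gives 21–31% for four PROMs and 23–37% for five. Both lie inside the 16–40% range above.

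**Not counted.** The article plans a per-protocol analysis and an intention-to-treat analysis with last value carried forward. Reading both adds further chances of a false positive.

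**The case against.** The strongest reply is that this is a self-described pilot with ranked outcomes. Full null and alternative hypotheses are written only for the primary tier, the lower tiers are introduced in softer language about potential differences, and testing secondary outcomes at a nominal .05 is common. The Results section states an expectation, not a decision rule. That is fair as far as it goes. But the same section of the article calls the lower-tier comparisons hypotheses to be tested, the analysis section applies the same alpha to all of them, and nothing labels them exploratory. The pilot label does not limit what may be claimed from them.

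Four stronger readings are tempting, and the article does not support them:

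- *A reader might infer that a false quality-of-life effect is likely.* For all PROMs together the chance is 16–40%, and for SF-12 alone at most about 10%. A chance above one half arises only with a tertiary count that the article does not state.
- *A reader might infer that there is no hierarchy at all.* Outcomes are ranked primary, secondary and tertiary. What is absent is a rule linking the tests.
- *A reader might infer that variables created during database exploration will be tested at .05 as tertiary hypotheses.* The Analyzed Data section says only that they will be calculated and reported. It does not separate them from prespecified outcomes either, so a clarifying sentence is worthwhile, but hypothesis status is not stated.
- *A reader might count the unnamed tertiary parameters, or the abstract's wording "Secondary outcomes will be the sum scores of patient-reported outcomes and relevant kinematic, kinetic, and spatiotemporal parameters", as faults in the analysis.* A parameter list is commonly left to the full protocol, and the abstract merges two lower tiers into one, which is an editorial mismatch.

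**Conclusion.** The concern holds in a limited form. Secondary and tertiary comparisons are set up as formal hypotheses at full alpha and at two visits. They have no gatekeeping and no exploratory label, and the stated reason for not adjusting does not apply to them. Under no true effect, the chance of at least one false-positive PROM result is about 16–40%, or 25–29% at an assumed correlation of 0.5, against .05 per test. The test counts for the PROMs come from the article; the correlations are assumptions. The tertiary range of 31–94% rests on an assumed 54 tests and illustrates scale only. The primary analysis, its estimates and the sample size are unaffected. What changes is how lower-tier findings may be interpreted, which makes this a change that should be made and not a fatal defect.

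**What to change.** 1. **Statistical Analysis:** delete the two-arm justification as it applies to the secondary and tertiary tiers.
2. **Study Goals and Statistical Analysis:** state that secondary and tertiary comparisons are exploratory, reported as estimates with 95% CIs and nominal P values, and that no claim of effectiveness will be based on them.
3. **Analyzed Data:** state that variables created during database exploration are post hoc, will be marked as such and will be reported descriptively.
4. **Results:** reword so that a confirmatory effect is expected only for the primary functional-deficit outcomes.

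The cost is wording only, with no extra patients, visits or data. The small downside is that a significant PROM or biomechanical result can no longer be presented as a confirmed effect.

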## Methods

### Trial Design

The study is set up as a pilot cluster-randomized controlled trial with 2 parallel groups. Patients will be recruited prior to surgery. At the time of recruitment, the HHS will be assessed routinely in the participating hospital. Additionally, all included patients will be equipped with an activity monitor (wGT3X-BT; ActiGraph LLC) for 2 days prior to surgery in order to assess their mobility level before THA. Baseline assessment will be conducted 4-6 weeks after surgery, and randomization will follow thereafter. During the active phase of 8 weeks, supervised group exercise therapy will take place in both groups. In addition, the IG will perform a home exercise program with the support of an RTF device. The CG will perform a comparable home exercise program without the support of an RTF device (home exercise program following written instructions). Follow-up assessments will take place as close as possible to 8 weeks after baseline and 6 months postsurgery. The schedule of the study is presented in Table 1.

**Table 1 table1:** Schedule of the study.

Schedule			Study period												
			Enrollment (t_–1_)^a^		Surgery		t_0_^b^		Allocation^c^		Intervention phase^d^		t_1_^e^		t_2_^f^
Eligibility screening			✓		—^g^		—		—		—		—		—
Informed consent			✓		—		—		—		—		—		—
2-day activity monitoring			✓		—		—		—		—		—		—
HHS^h^			✓		—		—		—		—		—		—
Allocation			—		—		—		✓		—		—		—
**Intervention**															
	RTF^i^ group	—		—		—		—		✓		—		—	
	CG^j^	—		—		—		—		✓		—		—	
**Assessments**															
	3D movement analysis	—		—		✓		—		—		✓		✓	
	Clinical status	—		—		✓		—		—		✓		✓	
	Body composition analysis	—		—		✓		—		—		✓		✓	
	7-day activity monitoring	—		—		✓		—		—		✓		✓	
	PROMs^k^	—		—		✓		—		—		✓		✓	

^a^Enrollment will be 4-10 days prior surgery.

^b^Baseline t_0_ is 4-6 weeks postsurgery.

^c^Randomized allocation will be conducted at the end of baseline assessment.

^d^8 weeks.

^e^3 months postsurgery.

^f^6 months postsurgery.

^g^Not applicable.

^h^HHS: Harris Hip Score.

^i^RTF: real-time feedback.

^j^CG: control group.

^k^PROM: patient-reported outcomes measure.

The number of participants assessed for eligibility, allocated to study arms, and analyzed will be recorded using the CONSORT (Consolidated Standards of Reporting Trials) extension flowchart on cluster randomized trials [23]. Figure 1 illustrates the trial design and participant flow through the trial. The protocol is according to SPIRIT (Standard Protocol Items: Recommendations for Interventional Trials) reporting guidelines [24].

**Figure 1 figure1:**
[figure not shown]
Flow diagram of the progress through the phases of the trial. CG: control group; IG: intervention group; PHO: paper handout; RTF: real-time feedback. *Eligibility based on clinical data.

### Sample Size Estimation and Study Population

As knowledge and studies concerning the effect of RTF on exercise following unilateral THA are missing, the sample size cannot be calculated based on given effect sizes. Therefore, the sample size for comparing 2 independent means was calculated using an estimated effect size (d) of 0.8. Assuming the planned 16 clusters with a cluster size of 3 participants each and an intracluster correlation of 0.05, a nominal sample size of 24 participants per group would give a power of 0.75 (α=.05). The effect size (d) of 0.8 and the intracluster correlation of 0.05 were estimated, and hence, the achieved power in this pilot cluster-randomized trial will be reported. The number of participants included in topic-specific studies range from 14 to 111 [5,11,14,25,26]. Considering a dropout of 30%, we will recruit 70 participants from the Orthopedic Hospital Speising, Vienna, Austria.

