#### Recruitment

Patients scheduled for elective unilateral THA at the Orthopedic Hospital Speising will be informed by their orthopedic surgeon of an opportunity to participate in the study. If interested, they will be checked for eligibility by physicians. One of the enrolling physicians is also acting as the principal investigator according to Austrian medicinal product law. In the case of willingness and eligibility of the potential participant, written informed consent will be obtained by the informing and enrolling physician from the participant prior to surgery. On the day of discharge, participants will be finally checked by a physician concerning their status of recovery with regard to the exclusion criteria.

Clusters for the intervention phase have been defined as groups of 2-5 patients starting their collective training program at the same time. Due to logistics, only 1 clustered group will be considered at a time. The group exercise program will be the same for both the IG and the CG and will only differ in the home exercise program, which for the IG will be supported by a digital real-time exercise feedback prototype for digitally guided training. Patients who belong to the same cluster will be randomized to receive the same treatment. Clusters after baseline assessment will be randomized in blocks (block size blinded) by means of an online random sequence generator [27] to achieve equal allocation of clusters to both arms. Due to the small number of clusters (about 20), no stratified randomization approach will be applied. Patients will be arbitrarily clustered based on the surgery date. Due to the nature of the studied conditions, it will not be possible to blind researchers.

Patients’ active participation will take 6 hours for assessments performed at baseline, 3-month, and 6-month follow-up. They will be offered a maximum of possible supervised exercise sessions of 24 hours and will be required to practice their home exercise program for 20 hours over the intervention period of 8 weeks. Shopping vouchers of €220 (US $239) will be offered as an incentive for participation.

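### The stated power of 0.75 ignores the few cluster-level degrees of freedom; without credit for baseline adjustment, 16 clusters of 3 give about 0.69, and their relation to the roughly 20 clusters to be randomised is not explained

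*Protocol article*

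**What the plan says.** The section Sample Size Estimation and Study Population describes a comparison of two independent means, "calculated using an estimated effect size (d) of 0.8". Its design inputs are: "Assuming the planned 16 clusters with a cluster size of 3 participants each and an intracluster correlation of 0.05". From these it concludes that "a nominal sample size of 24 participants per group would give a power of 0.75 (α=.05". It then allows for attrition: "Considering a dropout of 30%, we will recruit 70 participants". It also says that the effect size and the intracluster correlation are estimates and that the power achieved will be reported.

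The Recruitment section says that patients in a cluster all receive the same treatment and that clusters are randomised in blocks "to achieve equal allocation of clusters to both arms". It gives a cluster size of 2 to 5 and a different number of clusters: "Due to the small number of clusters (about 20), no stratified randomization approach will be applied".

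The Statistical Analysis section plans a linear mixed model with a random intercept for cluster, adjusted for each participant's own baseline value and for the cluster mean at baseline. P values are obtained "via the Satterthwaite degrees-of-freedom method", and the level is fixed thus: "The α value will be set to .05, and exact 2-sided" P values will be reported.

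**The concern.** The sample size section inflates the variance for clustering, but its result matches a calculation that treats that variance as known. The treatment contrast lies between clusters. Its error is therefore estimated from the variation among 16 cluster means, which leaves about 14 degrees of freedom. The critical value is then 2.14, not 1.96. The analysis section names a degrees-of-freedom method that takes this into account; the printed power does not.

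The stated chance of missing a true effect of 0.8 is 25%. If it is nearer 31%, a null result on any of the three primary outcomes is weaker evidence than the article suggests. The number of clusters drives both the degrees of freedom and the power, so it matters that two sections give different numbers without linking them.

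**Working it through.** **Inputs from the article.** d = 0.8; 16 clusters, 8 per arm; 3 patients per cluster, so 24 per arm; intracluster correlation 0.05; two-sided α = 0.05; 70 recruited with 30% dropout; about 20 clusters in the Recruitment section.

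**Reproducing the stated figure**
- Design effect = 1 + (3 − 1) × 0.05 = 1.10.
- Effective n per arm = 24 / 1.10 = 21.82.
- Noncentrality = 0.8 × √(21.82 / 2) = 2.642.
- Normal approximation: Φ(2.642 − 1.960) = 0.7525, the stated 0.75.

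**Same noncentrality, t distribution, no covariates**

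| Reference distribution | df | Power |
|---|---|---|
| Normal | – | 0.7525 |
| Individual-level t (2 × 24 − 2) | 46 | 0.735 |
| Cluster-level t (16 − 2) | 14 | 0.691 |

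Most of the loss comes from the cluster-level degrees of freedom (0.735 to 0.691), less from replacing z by an individual-level t (0.7525 to 0.735).

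**Simulation of the random-intercept test without covariates** (balanced design, 400,000 replicates). Power is 0.681 if the residual 46 df are used whenever the cluster variance is estimated as zero, and 0.665 if 14 df are kept throughout. That variance is estimated as zero in about 40% of replicates.

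**Effect of the planned baseline adjustment.** Two covariates cost up to 2 df, which leaves 12. If they remove no variance, or if d = 0.8 already refers to the adjusted SD, power with 12 df is 0.680. If d refers to the raw SD and the baseline-outcome correlation is r, the noncentrality becomes 2.642 / √(1 − r²). This takes the same proportional variance reduction between and within clusters. The values of r are assumptions; the article gives none.

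| Assumed r | Noncentrality | Power, 12 df | Power, 14 df |
|---|---|---|---|
| 0 | 2.642 | 0.680 | 0.691 |
| 0.3 | 2.770 | 0.720 | 0.731 |
| 0.4 | 2.883 | 0.754 | 0.765 |
| 0.5 | 3.051 | 0.800 | 0.810 |

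**Cluster counts**
- 16 × 3 = 48 analysed, and 48 / 0.7 = 68.6, so 70 recruited fits.
- 70 / 20 = 3.5 recruited per cluster, inside the range of 2 to 5.
- 70 × 0.7 = 49 completers; 49 / 20 = 2.45 per cluster. The design effect is 1 + 1.45 × 0.05 = 1.0725, effective n per arm is 24.5 / 1.0725 = 22.84 and noncentrality is 2.704. With 18 df, power is 0.725.
- Twenty full clusters of 3 (60 analysed) would give noncentrality 2.954 and, with 18 df, power 0.798.

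**The case against.** Four arguments on the other side deserve weight.

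**The arithmetic is sound.** Inflating a two-sample calculation by the design effect is a standard simplification, and it was carried out correctly. A reader might infer a slip, or that 0.75 can be approached only with a normal approximation. Neither follows: an individual-level t gives 0.735, within two points. What stands is that neither reference distribution suits a contrast between 16 randomised clusters.

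**The planned model is not the unadjusted one.** A reader might take 0.69 as the power of the planned analysis, and conclude that its type II error is 31%. The article does not support that. The same section that brings in the degrees-of-freedom penalty also brings in baseline adjustment, and a correlation of about 0.4 would bring power back to 0.75. This objection stands and limits the point to the basis on which the sample size section was written: two independent means, with no correlation mentioned.

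**The cluster counts may be compatible.** Sixteen clusters of 3 can be the evaluable sample, and about 20 the clusters formed from 70 recruits. It would be too strong to call this a contradiction, or to use it as evidence of lower power: 20 clusters with 49 completers give 0.725, more than 0.691. But losing individual patients mainly shrinks clusters and need not reduce 20 to 16, and the article does not say which count applies at which stage.

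**This is a pilot with guessed inputs.** The article admits this and promises to report the power achieved, and its formula may be set out in the full protocol. That covers uncertainty in the effect size and the intracluster correlation, and leaving the formula out is no fault in an article. It does not cover a printed figure that leaves out a feature of the design known in advance.

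**Conclusion.** The point holds in a limited form. On the sample size section's own inputs, without credit for baseline adjustment, power is about 0.69 with 14 cluster-level degrees of freedom (0.665 to 0.681 in simulation of the random-intercept test). The stated 0.75 is thus about 6 points too high on that basis.

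The power of the adjusted model cannot be fixed from the article. It is about 0.68 if adjustment brings no gain, and it equals or exceeds 0.75 if d is on the raw SD and the correlation is about 0.4 or higher. These figures assume equal cluster sizes and take the effect size and intracluster correlation as given. The two cluster counts are an unexplained input, not a demonstrated conflict. The point concerns how the planning figure is reported; it does not call the planned analysis into question.

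**What to change.** Choose one of two restatements in the sample size section:
- Give power of about 0.69 for 16 clusters of 3, and say that it uses cluster-level degrees of freedom and takes no credit for baseline adjustment.
- Or state the assumed baseline-outcome correlation, say whether the effect size of 0.8 is on the raw or the baseline-adjusted SD, and give the resulting power with the degrees of freedom left after the covariates.

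Add one sentence linking the 16 clusters of 3 to the roughly 20 randomised clusters, with the expected number and size of clusters before and after dropout. If 20 clusters averaging 2.45 completers is the expected position, the unadjusted figure is about 0.72.

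The cost is a few sentences and, on the first option, a slightly less favourable number. Neither the number of patients nor the planned analysis changes.
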